### Intervention

The trial will explore the impact of the Labinic synbiotic, composed of a prebiotic (BENEO Orafti Synergy1; 50% oligofructose/50% fructooligosaccharide, 200 mg) plus three live bacterial strains (*Lactobacillus acidophilus* NCFM, *Bifidobacterium infantis* Bi-26 and *B. bifidum* Bb-06; total of 5 billion organisms/dose (Biofloratech, Walton-on-Thames, Surrey, UK). The synbiotic supplement is a powder in capsules with one dose per capsule. The contents of the capsule can be sprinkled directly into the infant’s open mouth before feeding. Study staff will visit daily for 9 days after the initial dose and then weekly to age 6 months (32 doses in total) to supervise the administration of the synbiotic and record adherence. Administration will be repeated once if the infant vomits within 30 min of synbiotic administration. In infants taking antibiotics, including HIV-exposed infants taking daily co-trimoxazole, the synbiotic will be administered where possible at least 4 hours before/after the antibiotic or between doses to minimise the effect of the antibiotic on the synbiotic microbes. Antibiotic usage will be recorded during dosing visits and morbidity follow-up. Infants randomised to the control arm will receive the same follow-up as infants in the AASH observation cohort. All infants will receive routine care as per national guidelines and will have contact details and mobile phone numbers of study staff for assistance in case of infant illness.

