#### Primary outcome

The primary outcome of the trial is linear growth at age 12 months assessed by LAZ. Regularly calibrated equipment for anthropometry will include a Model 876 SECA/infant scale, UNICEF stadiometer/infantometer, Lufkin WP601 measuring tape and Holtain skinfold calliper. Measurements will be conducted in duplicate with a third measurement taken if the first two measurements do not agree within a specified amount. Weight will be recorded to the nearest 100 g and height, length, mid-upper arm circumference, head circumference, triceps and subscapular skinfolds, and knee-to-heel length to the nearest 0.1 cm. Measurements will be used to determine z-scores using the WHO growth standards for LAZ, weight-for-length (WLZ), triceps-for-age and subscapular-for-age. Children will be classified as stunted or wasted if their LAZ or WLZ is <−2 SDs, respectively.

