### Sample size determination

The sample size calculation is based on observing a clinically meaningful improvement in linear growth in the intervention arm. In the WASH Benefits study in Kenya, the control group (n=1431) at median age of 12 months (range 2–18 months) had a mean LAZ of −1.13 (SD=1.13).^5^ To observe a 25% improvement in LAZ at age 12 months (ie, LAZ=−0.8475, SD=1.13) with 80% power, α=0.05 and with 1:2 group allocation would require 189 infants in the intervention group and 378 in the control group. We plan to allow for 20% loss to follow-up by recruiting 236 to the intervention group and 472 to the control arm. Based on previous studies, we consider that this number of infants will also be sufficient to observe meaningful differences in biomarkers between the study arms.^8 10 12 20^

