### Statistical analysis

Analysis of the primary and secondary endpoints will be based on intention to treat. Mean/median values of biomarkers, the proportion of infants with abnormal biomarker concentrations, gut colonisation with enteropathogens and the proportion of infants/children with episodes of illnesses will be compared in the two arms at 1, 6 and 24 months. Additional analysis of the primary and secondary endpoints will also be presented according to adherence to synbiotic administration. Data will be analysed using generalised linear models with treatment as the only predictor, generating the estimates of treatment effects and their 95% CIs. For outcomes with repeated measurements, the linear model will have a binomial distribution and logit link function for binary outcomes and a normal distribution and identify link function for continuous outcomes. Mean differences between the two treatment arms together with 95% CIs will be derived from the appropriate linear model. Missing data will be treated as missing completely, and no imputation of primary or secondary endpoints will be made. Adjustment for covariates and inclusion of interaction terms will be performed as appropriate. More details on statistical analysis methods using secondary variables will be described in other papers in the supplement.

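### The primary analysis assumes data are missing completely and drops infants without a 12-month LAZ, leaving scheduled earlier lengths unused; this biases the result if loss is related to growth differently in the two arms

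*Protocol article*

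**What the plan says.** In the Protocol article, the Primary outcome section fixes a single time point: "The primary outcome of the trial is linear growth at age 12 months assessed by LAZ". The Statistical analysis section declares the principle, "Analysis of the primary and secondary endpoints will be based on intention to treat", then the model, "Data will be analysed using generalised linear models with treatment as the only predictor", and the missing-data rule, "Missing data will be treated as missing completely, and no imputation of primary or secondary endpoints will be made".

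Two further sentences in that section bear on the point. On covariates: "Adjustment for covariates and inclusion of interaction terms will be performed as appropriate". On longitudinal data: "For outcomes with repeated measurements, the linear model will have a binomial distribution and logit link function for binary outcomes", with a normal distribution and identity link for continuous outcomes. Neither names the primary outcome or a within-child correlation.

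The Sample size determination section says "We plan to allow for 20% loss to follow-up by recruiting 236 to the intervention group and 472 to the control arm". The Trial design section lists anthropometry at birth, 3 and 6 months before the 12-month visit. Table 1 marks non-weight anthropometry at 1, 3, 6 and 9 months before month 12, and not at birth. Months 3 and 6 appear in both.

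**The concern.** The rule, the model and the single-visit outcome together leave a complete-case comparison. An infant measured at 3 and 6 months and then lost contributes nothing to the primary result, although those lengths carry information about the missing 12-month value.

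The words *at random* are not printed after *missing completely*, but missing completely at random is the natural reading, and it is the strongest assumption available. Illness, death and migration are credible reasons for loss that relate to growth. The trial is open label, so loss could also differ between arms. If both happen, the difference in LAZ mixes the effect of the synbiotic with the effect of who stayed.

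**Working it through.** **Reproducing the plan's figures.** Inputs from Sample size determination: SD 1.13, means −1.13 and −0.8475 (difference 0.2825, or 0.25 SD), 80% power, α 0.05, allocation 1:2.

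- Intervention arm, normal approximation, two-sided: (1 + 1/2) × (1.960 + 0.842)² / 0.25² = 188.4. The t-based calculation gives 189.0, hence 189 and 378, as stated.
- Loss allowance: 189/0.8 = 236.25 and 378/0.8 = 472.5, stated as 236 and 472.
- Infants without a 12-month LAZ if the allowance is reached: 708 − 567 = 141 (47 intervention, 94 control).
- Standard error at 189 and 378: 1.13 × √(1/189 + 1/378) = 0.1007. Power with no bias: 80.1%.

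**Bias of a completers' comparison.** Let d be the proportion lost in an arm and g the mean LAZ of retained minus lost infants in that arm. The retained mean exceeds the full-arm mean by d × g. So:

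bias (intervention − control) = d_I × g_I − d_C × g_C.

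With the same d and g in both arms this is zero, whatever the total loss.

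**Illustration 1: unequal loss, same gap.** The document gives neither arm-specific loss nor gaps, so these are assumptions. Controls are taken to lose more infants, with lost infants shorter, so the bias is negative. Power is at a true effect of 0.2825; the last two columns are at no true effect. All use SE 0.1007.

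| Difference in loss | Gap (LAZ) | Bias (LAZ) | Share of 0.2825 | Power | Rejects in favour of control | Rejects in favour of synbiotic |
|---|---|---|---|---|---|---|
| 0 | any | 0 | 0% | 80% | 2.5% | 2.5% |
| 5 points | 0.3 | −0.015 | 5% | 76% | 3.5% | 1.7% |
| 5 points | 1.0 | −0.05 | 18% | 64% | 7.2% | 0.7% |
| 10 points | 0.3 | −0.03 | 11% | 71% | 4.8% | 1.2% |
| 10 points | 0.5 | −0.05 | 18% | 64% | 7.2% | 0.7% |
| 10 points | 1.0 | −0.10 | 35% | 44% | 16.7% | 0.2% |

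Example: 0.10 × 0.5 = 0.05; 0.05/0.2825 = 18%; power = Φ((0.2825 − 0.05)/0.1007 − 1.96) ≈ 64%.

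**Illustration 2: equal loss, different gap.** With 20% lost in both arms, no gap in the intervention arm and a gap of 0.25 or 0.5 SD in controls, bias = −0.20 × 0.25 × 1.13 = −0.057, or −0.20 × 0.5 × 1.13 = −0.113 (20% or 40% of the target). Power falls to 61% or 39%. Equal loss rates alone are therefore not a safeguard. Erasing the whole effect at 20% loss would need gaps differing by 0.25/0.20 = 1.25 SD between arms.

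**Does using earlier lengths help?** In a simulation, loss depended on an earlier LAZ, whose correlation with 12-month LAZ was assumed to be 0.5, 0.7 or 0.85. When that dependence or the loss rate differed by arm, completers' bias was about −0.05 to −0.22 LAZ. Regression on the earlier LAZ within arm brought it to at most 0.003 in absolute value. With the same mechanism and loss rate in both arms, completers' bias was about zero.

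**The case against.** **Contact between arms.** A reader might infer that the dosing visits make thinner follow-up, and so heavier loss, likely in controls. The Intervention section does say "Infants randomised to the control arm will receive the same follow-up as infants in the AASH observation cohort". But the Trial design section and Table 1 schedule weekly morbidity assessment to 24 months without distinguishing arms. After the daily doses of the newborn period, dosing visits are weekly too, and they end six months before the primary endpoint. Differential loss remains possible in an open-label trial, but the document does not show it. This stands.

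**The 20% itself.** A reader might infer that the planned loss biases the result. It does not: it is a recruitment allowance, and bias is about zero if the mechanism is the same in both arms. Every magnitude above rests on assumed arm differences. This stands.

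**False claims of benefit.** A reader might take an inflated error rate, up to 17% in the table, as a risk of wrongly declaring benefit. If controls lose more poorly growing infants, nearly all those rejections favour control, and false claims of benefit fall below 2.5%. The cost is mainly power. This stands for that direction of loss; the document does not fix the direction.

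**Unseen analysis plan and labels.** The article leaves room for covariate adjustment and mentions repeated measurements, and a separate plan may add sensitivity analyses; their absence here is not the point. Analysing available outcomes by randomised arm is also often called intention to treat, so the label alone is not an error. But the missing-data rule is printed, it bars imputation of the endpoints, and neither permissive sentence commits the primary analysis to earlier LAZ. That part of the objection does not remove the point.

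**Conclusion.** The point holds as a should-fix. The article states a rule, rather than leaving a gap, that rests the primary result on the strongest missing-data assumption and sets aside lengths already scheduled for up to 141 of 708 infants. Bias arises only if loss relates to growth differently by arm, through unequal rates or unequal dependence. Under the assumed 5 to 10 point differences in loss and gaps of 0.3 to 1.0 LAZ, it is 0.015 to 0.10 LAZ, or 5% to 35% of the target. The document supports neither a claim that the trial will be biased nor a claim that the synbiotic will be favoured.

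**What to change.** Replace the assumption of data missing completely with a primary analysis valid under missing at random:

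- Fit a likelihood-based mixed model of LAZ at the scheduled visits up to 12 months, with treatment-by-visit and clinic terms, and take the treatment difference at 12 months. Use at least months 3, 6 and 12. Add birth, month 1 and month 9 where length is measured, once the Trial design text and Table 1 have been reconciled.
- Amend the treatment-only wording to match.
- Report loss and deaths by arm. State that the estimate does not define LAZ for infants who died, since the model implicitly extrapolates to 12 months for them.
- Limit the no-imputation rule to the primary analysis, so that one missing-not-at-random sensitivity analysis can be run, for example delta-adjusted multiple imputation by arm.

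The cost is a change of wording and modest programming. Sample size and visits do not change. The analysis would then rely on missing at random, which is still an assumption but weaker than the present one.

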### Patient and public involvement

There was no involvement of patients or the public in the design of this trial.

### Protocol version

The protocol version is V.2.0, 12 June 2020.

## Discussion and conclusion

Childhood stunting affects many children in vulnerable populations, particularly in Africa, while interventions targeting WASH and nutrition have had limited success improving linear growth. Evidence has accumulated for suboptimal gut health and EED contributing to early life growth faltering. This clinical trial aims to evaluate the effectiveness of a synbiotic in improving linear growth in early life, as a potential affordable and scalable public health intervention.

There are many potential prebiotic, probiotic and synbiotic preparations on the market, with different mixtures of substrates and micro-organisms. However, the limited knowledge of their effects on the gut complicates the selection of specific products for evaluation in clinical trials, including for the prevention or amelioration of EED. Identifying probiotics with specific antipathogen properties relevant to EED is difficult given the limitations of in vitro and animal models in mimicking the complex environment of the infant’s gut and the numerous enteropathogens that may contribute to EED.^10^ Colonisation resistance is mediated through multiple mechanisms, and some are likely shared among *Lactobacillus* and *Bifidobacterium* species, including production of fermentation acids and acidifying the gut lumen.^15^ Probiotics may have additional beneficial effects in EED through reducing intestinal inflammation and permeability.^21^ Prebiotics may supplement human milk oligosaccharides, the natural prebiotics in breast milk, with additional carbon sources to promote the growth of putatively beneficial microbes such as bifidobacteria.^22^ Prebiotics may also serve as decoy receptors for enteropathogens.^23^

Lactobacilli and bifidobacteria are supplied routinely to about 70% of preterm infants nursed in neonatal units in Germany,^24^ based on their potential to prevent necrotising enterocolitis^18^ and late-onset sepsis.^5^ A recent survey reported that Labinic was used routinely in preterm infants in seven neonatal units in the UK.^25^ The Labinic probiotic has been associated with a significant decrease in necrotising enterocolitis and late-onset sepsis in preterm infants with no episodes of sepsis due to *Lactobacillus* or *Bifidobacterium.*
20 In addition to evaluation in the SENGSYN trial, we are liaising with the research team of the ongoing PROSYNK study in western Kenya (Pan Africa Clinical Trial Registry, PACTR202003893276712) to allow a comparison of the effects of the Labinic synbiotic in two different settings.

Despite the widespread and apparently safe use of probiotics in highly susceptible individuals, adverse effects of an administered *Lactobacillus* have been reported in sick children receiving intensive care.^21^ Although we are not recruiting sick children in this study, we will closely monitor SAEs.

We will start the intervention within the first 3 days of life to limit competition from other gut organisms that rapidly start to colonise the gut following birth. Administration will discontinue at 6 months as the introduction of complementary food is associated with a marked increase in diversity of the gut microbiota,^14^ likely reducing the effects of prebiotics, probiotics and synbiotics.

The same procedures that will be undertaken in all infants participating in the AASH cohorts, including the assessment of feeding and WASH practices, epigenetic status and characterisation of the gut microbiota, will also be undertaken in infants receiving the synbiotic in this study. This will provide a valuable opportunity to explore how synbiotic administration interacts with other domains and the mechanisms through which it may affect growth.

The SENGSYN study will establish an infrastructure in rural Senegal for evaluating alternative prebiotic, probiotic and synbiotic products and other potential approaches to modulate the gut microbiota in early life. This study will also further develop our understanding of the utility of the selected biomarkers in the evaluation of EED, which may allow us to test a series of novel interventions efficiently in advance of large-scale clinical trials.

## Data Availability

Data sharing not applicable as no datasets generated and/or analysed for this study.
